# Do cognitive measures and brain circuitry predict outcomes of exercise in Parkinson Disease: a randomized clinical trial

**DOI:** 10.1186/s12883-015-0474-2

**Published:** 2015-10-24

**Keywords:** Parkinson’s disease, Exercise, Brain imaging, and cognition

## Abstract

**Background:**

There is emerging research detailing the relationship between balance/gait/falls and cognition. Imaging studies also suggest a link between structural and functional changes in the frontal lobe (a region commonly associated with cognitive function) and mobility. People with Parkinson’s disease have important changes in cognitive function that may impact rehabilitation efficacy. Our underlying hypothesis is that cognitive function and frontal lobe connections with the basal ganglia and brainstem posture/locomotor centers are responsible for postural deficits in people with Parkinson’s disease and play a role in rehabilitation efficacy. The purpose of this study is to 1) determine if people with Parkinson’s disease can improve mobility and/or cognition after partaking in a cognitively challenging mobility exercise program and 2) determine if cognition and brain circuitry deficits predict responsiveness to exercise rehabilitation.

**Methods/Design:**

This study is a randomized cross-over controlled intervention to take place at a University Balance Disorders Laboratory. The study participants will be people with Parkinson’s disease who meet inclusion criteria for the study. The intervention will be 6 weeks of group exercise (case) and 6 weeks of group education (control). The exercise is a cognitively challenging program based on the Agility Boot Camp for people with PD. The education program is a 6-week program to teach people how to better live with a chronic disease. The primary outcome measure is the MiniBESTest and the secondary outcomes are measures of mobility, cognition and neural imaging.

**Discussion:**

The results from this study will further our understanding of the relationship between cognition and mobility with a focus on brain circuitry as it relates to rehabilitation potential.

**Trial registration:**

This trial is registered at clinical trials.gov (NCT02231073).

## Background

Falls due to balance and gait impairments are one of the most important health and quality of life issues in the elderly. Parkinson Disease (PD) is responsible for more falls than any other chronic disease and imposes a heavy burden on over 3 % of people over 65 years [1]. Until recently, gait and balance were largely perceived as automated, biomechanical processes that did not require cortical control. However, work over the past decade has demonstrated the important relationships between balance/gait/falls and cognition [2, 3]. In fact, 60 % of older people with cognitive impairment fall annually, approximately twofold more than cognitively intact peers, and the worse the cognitive deficits, particularly executive dysfunction, the more often people fall [4–6]. These studies support the notion that mobility and cognition are connected, perhaps because mobility relies upon common cortical-subcortical networks subserving cognition and balance. Executive function, defined as a set of higher order cognitive processes that control, integrate, organize and maintain other cognitive abilities, is often altered in people with PD. [7–9] Specific deficits include response inhibition, set switching and updating of working memory [10–12]. All of these executive components are required for functional mobility in everyday environments and the relationship between such function with balance and rehabilitation has not been explored in people with PD [2, 13].

Imaging studies also suggest a link between structural and functional changes in the frontal lobe (a region commonly associated with cognitive function) and mobility. A recent European study of 415 older people used diffusion tensor imaging (DTI) to show that parkinsonian signs of slow walking speed, and falls are related to white matter loss in the frontal cortex, but not the basal ganglia [14–16]. Likewise, a recent systematic review that included eighty-six published studies using various imaging modalities to relate neuroimaging to mobility reported that there were consistent finding across imaging modalities linking frontal lobe measures with mobility performance [17]. Specifically, this targeted review supports an increased cortical control of gait in aging, reduced volume in several regions of grey and white matter that relate to impaired mobility and consistent neuroimaging findings that reveal the basal ganglia, parietal and frontal cortices and cerebellum are related to mobility outcomes [17]. Recent work identifying the locomotor neural network, which includes the i) supplementary motor area, ii) subthalamic nucleus, iii) mesencephalic and iv) cerebellar locomotor regions, also provides evidence for reduced structural and altered functional connectivity in people with PD [18, 19].

Though mobility and cognitive function may be related, rehabilitation of such deficits typically remains separate. There is some evidence that cognitive training may improve motor function and that mobility training may improve cognitive function in the elderly but a recent meta-analysis on this topic revealed limited and low quality studies [20]. Although many individual studies of exercise and rehabilitation interventions report success in improving balance and gait in people with PD, the overall effect size of many interventions are sometimes minimal, often not reaching the minimally important change and/or minimal detectable change levels [20–25]. The limited success of rehabilitation treatment for mobility problems in people with PD may be because current physical therapy treatment does not directly address deficits related to frontal cortex dysfunction, such as cognition and cognitive control of balance and gait.

We recently documented that rehabilitation using the Agility Boot Camp (ABC) training resulted in multiple improvements in mobility such as turning, gait speed, sit-to-stand, and balance in people with PD. [26] With our increasing interest in the interaction of cognition and mobility, we adapted the ABC program to incorporate additional cognitive, particularly executive function, challenges known to be impaired in people with PD, now called Agility Boot Camp-Cognition (ABC-C). The purpose of this study is to 1) determine if people with PD can improve mobility and/or cognition after partaking in the ABC-C program compared to a control intervention of education and 2) determine if cognition and postural, cognitive, and brain posture/locomotor circuitry deficits predict responsiveness to the cognitively challenging Agility Boot Camp (ABC-C) rehabilitation. Our underlying hypothesis is that frontal lobe connections with the basal ganglia and brainstem posture/locomotor centers play a large role in postural deficits in people with PD and that postural impairments will be related to executive cognitive impairments. We will also determine which postural, cognitive and circuitry impairments predict efficacy of cognitively-challenging mobility rehabilitation.

## Methods/design

The study is a cross-over, randomized, controlled trial design to determine responsiveness to the ABC-C exercise program. The study will include 120 people with PD (Fig. 1). People will be randomized into either an exercise (case) or education (control) 6-week intervention period. They will cross over after 6 weeks to receive the other treatment. Both interventions were designed to have the same frequency and will be delivered by the same exercise trainers for all sessions. Preceding the interventions, all patients will be tested on multiple measures of mobility cognition, and imaging. This same battery of tests will be administered after 6 weeks of intervention before the participants cross over into the second intervention. A final assessment will occur at the end of the second and final treatment arm (Table 2). All other interventions (medication, other interventions, exercise) will be kept as stable as possible and any changes in medication will be monitored. This trial is registered at clinical trials.gov (NCT02231073) and OHSU ethics committee has approved all aspects of the study. All research is in compliance with the Helsinki Declarations.

**Fig. 1 Fig1:**
[figure not shown]
Consort diagram

### Participants

Inclusion criteria for PD recruitment are a) ages 50–90 years old, without major musculoskeletal or peripheral or central nervous system disorders (other than PD) that could significantly affect their balance and gait, b) no recent changes in medication, excessive use of alcohol or recreational drugs, c) no history of structural brain disease, active epilepsy, stroke or acute illness, factors affecting gait such as severe joint disease, weakness, peripheral neuropathy with proprioceptive deficits, severe peripheral vascular occlusive disease, severe musculoskeletal disorders, uncorrected vision or vestibular problems, or dementia that precludes consent to participate or ability to follow testing procedures, d) ability to stand or walk for 2 min with or without an assistive device, e) no medical condition that precludes exercise, f) no claustrophobia, severe tremor, or any health history (implanted devices, Deep Brain Stimulation, etc.) that would interfere or put the subject at risk near the powerful magnetic field of the MRI scanner. Though the majority of participants will have the diagnosis of idiopathic PD a subset of people with frontal gait disorder may be included for pilot data analysis. Participants will also be assessed at baseline on the Montreal Cognitive Assessment as a global screening of cognition. All subjects will be tested at Oregon Health & Science University. All subjects will sign an informed consent and no minors will be included in the study.

### Idiopathic PD inclusion criteria

The United Kingdom Brain Bank criteria will be used. i.e., bradykinesia and at least one of the following: rest tremor (4–6 Hz), muscular rigidity, and postural instability not cause by visual, vestibular, cerebellar or proprioceptive dysfunction. Three or more of the following must be present for diagnosis of idiopathic PD: unilateral onset, rest tremor, progressive, persistent asymmetry, excellent response to levodopa, levodopa-induced dyskinesia [27]. All PD subjects will be Hoehn and Yahr Levels II-IV and responsive to levodopa.

### Sample Size

We computed power to detect differences between the intervention arms in a crossover trial via analysis of variance with level of significance set to 0.05 (SAS software v9.3). We assumed baseline levels and patterns of change similar to those reported in King 2013 [28]. We examined the significance of treatment effect from 1000 simulated replications of a crossover trial. The trial is comfortably powered (85 %) with 120 patients if total Mini-BESTest score increases by 2.4 points on average in the ABC arm, and only 1.3 points on average in the control arm. We predict a roughly 20 % drop-out rate, which is conservative based on our previous experience with short duration trials of rehabilitation in PD and by others [24, 25, 28, 29].

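### The 85 % power is tied to 120 patients, which is also the enrolment figure, and no allowance is shown for the predicted 20 % drop-out; read as written, about 96 completers give about 76 % power

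*Protocol article*

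**What the plan says.** All the relevant statements are in the protocol article.

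- **Power (Sample Size).** "The trial is comfortably powered (85 %) with 120 patients", on condition that "total Mini-BESTest score increases by 2.4 points on average in the ABC arm, and only 1.3 points on average in the control arm". The difference to be detected is therefore 1.1 points.
- **Method (Sample Size).** "We computed power to detect differences between the intervention arms in a crossover trial via analysis of variance", at the 0.05 level; sidedness is not given. The figure comes from simulation: "We examined the significance of treatment effect from 1000 simulated replications of a crossover trial".
- **Inputs (Sample Size).** Baseline levels and patterns of change are borrowed from an earlier study. No standard deviation or within-patient correlation is printed, and attrition is not named among the inputs.
- **Drop-out (Sample Size).** Directly after the power figure: "We predict a roughly 20 % drop-out rate", which the authors describe as a cautious figure.
- **Enrolment (Methods/design).** "The study will include 120 people with PD".
- **Analysis (Statistical Analysis).** Improvement in the Mini-BESTest is compared by ANCOVA, adjusting for age and baseline score. The treatment effect is the change in the exercise period against the change in the education period. The section neither restricts the analysis to completers nor says how drop-outs are handled.

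**The concern.** The number powered and the number enrolled are the same, yet a fifth of those enrolled are expected to leave. Normally a planned number either carries an allowance for loss or has its power quoted for what remains after loss. Here a reader sees neither.

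A patient contributes the full crossover contrast only with the baseline, mid and final tests. Someone lost in the second period contributes less, and someone lost before the mid test contributes no change score. Randomisation follows phone screening and so can precede the clinic visit, which makes a loss of the second kind possible.

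At stake is how a null Mini-BESTest result would be read. A chance of missing a true 1.1-point difference of 15 % is not the same as one of about 24 %, and the wording of the power statement (*comfortably*) invites the more favourable reading.

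**Working it through.** **Inputs.** From Sample Size: difference 2.4 − 1.3 = 1.1 points; level 0.05; power 0.85; N = 120; drop-out 20 %; 1000 replications. From Methods/design: 120 enrolled. Assumed: a two-sided test and equal allocation to the two sequences.

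**1. The plan's own figure.** It cannot be reproduced, because no standard deviation is printed. It can be solved backwards. With SD the standard deviation of the within-patient difference between the two changes,

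power = Φ(1.1 × √N / SD − 1.960).

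At 85 % the non-centrality is 1.960 + 1.036 = 2.996, so SD = 1.1 × √120 / 2.996 = 4.02 points (3.99 with a non-central t on 118 df).

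**2. Applying the predicted drop-out.** Completers: 120 × 0.8 = 96. The non-centrality scales with √N, so the unprinted SD cancels:

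2.996 × √(96/120) = 2.680; power = Φ(2.680 − 1.960) = Φ(0.720) = 76.4 %.

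The non-central t gives 76.3 %; a one-sided 0.05 test gives 77.4 %. The type II error goes from 15 % to about 24 %.

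**3. Simulation error in the 85 %.** Standard error = √(0.85 × 0.15 / 1000) = 0.0113, so the 95 % range is 82.8 to 87.2 %. Carried through step 2, this gives 73.9 to 79.1 %.

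**4. Drop-outs who supply first-period data.** Suppose all 24 drop-outs leave after the mid test, 12 per sequence, and their first-period change is analysed. With ρ the correlation between a patient's two changes, the variance of one change is SD² / [2(1 − ρ)]. The 24 patients then add information 12(1 − ρ) / SD², so the effective number of completers is 96 + 12(1 − ρ). The document gives no ρ; the range below is assumed.

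| ρ (assumed) | Effective N | Power |
|---|---|---|
| 0.5 | 102 | 78.9 % |
| 0 | 108 | 81.1 % |
| −0.5 | 114 | 83.2 % |

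**5. Less drop-out.** At 10 %, with 108 completers only: Φ(2.996 × √0.9 − 1.960) = 81.1 %.

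**6. The other reading.** If the simulated trials already lost 20 %, then 85 % belongs to 96 completers. The implied SD is 1.1 × √96 / 2.996 = 3.60, and 120 complete patients would give Φ(2.996 × √1.25 − 1.960) = 91.8 %. On this reading there is no shortfall.

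**The case against.** The tempting stronger reading is that the trial simply has 76 % power and the printed 85 % is wrong. The document does not support this, for four reasons.

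- **The simulation may have included drop-out.** A simulated crossover can remove patients, and the 20 % stands in the sample-size paragraph straight after the power figure, where a planning input might stand. Without an SD, the 85 % cannot be assigned to 120 or to 96 complete patients. The flow diagram, which might show expected numbers, is not available. This stands, and it makes the 76 % conditional. Against it, the paragraph lists what went into the simulation and attrition is not on the list, so the unadjusted reading is the more natural one.
- **Drop-outs need not contribute nothing.** A reader might infer that only patients with all three tests can enter the analysis. The Statistical Analysis section does not say so, and a mid test is planned for everyone. This stands too, but even if every drop-out left after that test, power would recover only to about 79 to 83 %.
- **The 20 % may be pessimistic.** The authors suggest as much. At 10 %, completers-only power is still 81 %.
- **The planned model differs from the powered one.** Power was computed by analysis of variance, whereas the analysis adjusts for age and baseline score. The adjustment may change the residual variance, but the document claims no gain from it and does not use it to offset attrition.

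It may also be said that an article leaves such detail to the full protocol or the analysis plan. That would excuse a missing description of the simulation. It does not excuse printing N, power, effect and attrition side by side without saying how they fit together.

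**Conclusion.** The point holds in conditional form. If the 85 % refers to 120 patients with complete data, the predicted 20 % drop-out brings power for a 1.1-point difference to about 76 % on completers. The allowances in steps 3 to 5, taken one at a time, run from about 74 to 83 %, all below the stated figure. The rescaling does not depend on the unprinted SD. It does rest on a two-sided test, on power that scales with the square root of the number analysed and, for the 79 to 83 %, on the assumed correlations.

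If drop-out was already simulated, the 85 % is right and only its description is incomplete. Confidence that the text needs correcting is good; confidence that the true figure is 76 % is moderate.

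**What to change.** Look in the simulation code for whether patients were removed, then change one sentence in Sample Size.

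- **If no drop-out was simulated:** state that power for a 1.1-point difference is about 76 % with 96 completers and 85 % only if all 120 complete, and drop the word *comfortably*. If first-period data from drop-outs will be analysed, rerun the simulation with them and quote that result.
- **If 20 % were already removed:** state that 85 % refers to about 96 completers of 120 enrolled.

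Keeping 85 % on completers under the first case would take 120 / 0.8 = 150 enrolled, but correcting the statement does not require this. No change to enrolment, design or analysis is needed. The only cost, in the first case, is a less favourable stated power.

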### Randomization and blinding

Subjects will be randomly assigned per centralized database; Research Electronic Data Capture (REDCAP) to either Education (ED) or Exercise (EX) first after passing the phone screening procedure. A computerized block randomization in will be centrally held in the redcap database-scheduling mode. Randomization will be implemented by an independent statistician using a block size of twelve subjects. The exercise trainer (unblinded) will notify the subjects by phone. The researchers who will be performing all pre, mid and post-tests will remain blinded to group assignment throughout the duration of the study.

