#### Assessment procedures

All people who are eligible per phone screening will come into the clinic for the informed consent process. An investigator will verbally explain the consent form, allow the person ample time to ready through the consent form and then will acknowledge consent by signing the form. All subjects will first read and sign consent forms. All outcomes will be measured in the practical OFF levodopa state (12 hours withdrawal). At baseline, people will be assessed on imaging, mobility and cognitive measures and will repeat the mobility and cognitive measures after the 1st six-week intervention and again after the 2nd six-week intervention (Table 2).

**Table 2 Tab2:** Secondary outcome measures by domains

Domain Tested	Test	Description
Clinical		
	MDS-UPDRS	All sections of the Unified Parkinson’s Disease Rating Scale will be used to measure related to severity of PD.
	NFOGQ	The New FoG of Gait Questionnaire will be used to identify ‘freezers’ (score >3).
	Activities of balance confidence (ABC)	The ABC measures how balance confidence limits participating in the community.
	PDQ-39	This 39 item questionnaire measures multiple domains of quality of life.
Mobility		
	Balance	Postural sway during 30 seconds of quiet stance with and without cognitive task
	Turning	Smoothness of turning measured during the 1 min turning in place (360 degree turning in place) and turns during the 2 min walk with and without a cognitive task.
	Gait	Spatial and temporal gait metrics during walking with and without dual task
Imaging		
	High angular resolution diffusion imaging	High angular resolution diffusion imaging to assess white matter microstructure. Structural connectivity of the locomotor network will be assessed using probabilistic tractography.
	rsfcMRI	An indirect assessment of communication between spatially disparate neural regions. Analysis is restricted to neural regions comprising the locomotor network including the supplementary motor area, subthalamic nuclei, mesencephalic locomotor regions (pedunculopontine and cuneiform nuclei), and the midline cerebellar locomotor region
Cognition		
General	Scales for outcome of Parkinson’s Disease-Cognition (SCOPA-COG)	An instrument that was designed to assess the specific ‘frontal-subcortical” cognitive deficits found in Parkinson’s disease
Inhibition	Stroop task, flankers, Go/nogo, Stop signal task	The ability to deliberately inhibit dominant or prepotent responses when appropriate.

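### Allocation is triggered by the phone screen, apparently before consent and baseline testing, and the protocol does not say when patients learn their sequence

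*Protocol article*

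**What the plan says.** Four parts of the Protocol article bear on the order of events.

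- **Allocation** (Randomization and blinding): subjects are assigned in REDCap "to either Education (ED) or Exercise (EX) first after passing the phone screening procedure". The process is central: "Randomization will be implemented by an independent statistician using a block size of twelve subjects". No other trigger is given.
- **Notification** (same section): "The exercise trainer (unblinded) will notify the subjects by phone". This gives the messenger and the route, but not the time.
- **Consent and baseline** (Assessment procedures): "All people who are eligible per phone screening will come into the clinic for the informed consent process". There, "All subjects will first read and sign consent forms", and then "At baseline, people will be assessed on imaging, mobility and cognitive measures".
- **Eligibility** (Participants; Idiopathic PD inclusion criteria): the list includes Brain Bank signs, proprioceptive deficit and dementia severe enough to preclude consent. It also requires that "All PD subjects will be Hoehn and Yahr Levels II-IV and responsive to levodopa". On cognition, "Participants will also be assessed at baseline on the Montreal Cognitive Assessment as a global screening of cognition", with no cut-off. No separate visit for confirming eligibility is described.

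The Statistical Analysis section adjusts the Mini-BESTest comparison for age and baseline Mini-BESTest, defines the effect as change during ABC-C against change during control in either period, and promises a check of period-by-treatment interaction.

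**The concern.** If allocation comes first, anyone who then declines consent or is found ineligible at the clinic belongs to the randomised set but contributes nothing. They have no baseline covariate, no first-period change and, without consent, no follow-up. No analysis can restore them.

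If the trainer's call also comes before the clinic visit, two further routes open. Willingness to continue may depend on whether the patient has been told exercise first or education first. Patients may also sit the baseline tests knowing what comes next, and that could change their effort. Either would make the two sequences differ for reasons other than chance, and the promised interaction check relies on comparing the sequences.

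**Working it through.** **1. Order of events.** Allocation and the clinic visit are both anchored to the phone screen. Allocation needs nothing else. Consent needs a later visit, and baseline tests follow consent at that visit. The natural reading is: phone screen, allocation, consent, baseline. The Methods/design opening says testing precedes the interventions, which places baseline before the first class but not before allocation. The time of the trainer's call cannot be derived from the text.

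**2. The plan's own figure.** Sample Size states 85% power with 120 patients for gains of 2.4 and 1.3 points, a difference of 2.4 − 1.3 = 1.1. No SD is given, so the 85% cannot be reproduced. Solving backwards with a normal approximation (two-sided 0.05 assumed):

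SD of the within-patient difference = 1.1 × √n / (1.960 + 1.036)

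- all 120 analysed: 1.1 × 10.954 / 2.996 = 4.02
- 96 analysed (120 × 0.8, if the 20% drop-out is already inside the 120): 1.1 × 9.798 / 2.996 = 3.60

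**3. Precision.** The pre-baseline loss is not stated. Assuming 5 to 15% of 120, it is 6 to 18 people. Power = Φ(1.1 × √n / SD − 1.960):

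| SD | n analysed | Power |
|---|---|---|
| 4.02 | 120 | 85.0% |
| 4.02 | 108 (10% lost) | 81.1% |
| 4.02 | 102 (15% lost) | 78.9% |
| 3.60 | 96 | 85.0% |
| 3.60 | 84 (12 more lost) | 80.0% |

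**4. Bias from selective loss.** Let u be a standard-normal patient trait, and suppose the top fraction f is lost from one sequence only. The mean of u among those retained there is −φ(q)/(1 − f), where q is the (1 − f) quantile. The crossover estimate averages the two within-sequence differences, so only half of any shift in one sequence reaches it.

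- If u affects only the level of the score, it cancels within the patient and bias is 0.
- If u changes the period difference or the treatment effect by 1 point per SD (assumed), absolute bias is half the shift in mean u:

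| f | Mean of u retained | Absolute bias (points) | Share of 1.1 |
|---|---|---|---|
| 5% | −0.109 | 0.054 | 5% |
| 10% | −0.195 | 0.097 | 9% |
| 20% | −0.350 | just under 0.175 | 16% |

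A parallel comparison of period 1 alone would carry twice this bias.

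**5. Bias from a shift at baseline only.** This matters only if patients are told before baseline. With scores B (baseline), M (after period 1) and F (final), the within-patient effect is (M − B) − (F − M) = 2M − B − F when exercise comes first, and (F − M) − (M − B) = F − 2M + B when education comes first. Averaged over sequences, B has weight −1/2 in one and +1/2 in the other. If knowledge of the sequence moves baseline by d points more in one sequence, the unadjusted effect moves by d/2. An assumed d of 0.5 gives 0.25 points, or 0.25/1.1 = 23%. Adjusting for baseline changes this figure but does not guarantee its removal.

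**The case against.** **The order is inferred.** Neither section says outright that allocation precedes consent; both refer only to the phone screen. The CONSORT diagram (Fig. 1) was not visible in the text reviewed and may settle it. This stands as a caution, but the prose offers no later trigger.

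**Early notification is not stated.** A reader might infer that patients are told their sequence before consent and baseline. The protocol does not say so, and a call after baseline testing fits the text equally well. If patients have not been told, refusal cannot respond to allocation and baseline effort cannot be coloured by it. Loss unrelated to sequence costs precision only. This stands in full: the fault is that the timing is left open.

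**Failures at the clinic may be few.** A reader might infer a formal in-person eligibility step with many exclusions. None is described, the MoCA has no cut-off, most MRI items can be asked by phone, and diagnosis and stage may be known from records. That some criteria need an examination is a reasonable inference from their nature, but the number failing is unknown.

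**The design limits the damage.** Every patient receives both treatments, and education first delays exercise by six weeks without denying it. Differences in score level cancel. This stands against any claim that both sequences are necessarily biased. It does not cover loss tied to period change or treatment response, or a shift at baseline alone.

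**Safeguards exist.** Central allocation and blinded assessors protect concealment and scoring. They do not prevent loss after allocation or act on patient expectation.

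**Conclusion.** The concern holds in a limited form. The phone screen is the only stated trigger for randomisation, consent and baseline apparently follow it, and the time of notification is not given. Patients can therefore be randomised and then lost without the baseline score that the ANCOVA needs. If they are told early, these losses and baseline performance could differ by sequence.

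Bias in the treatment contrast is possible and probably modest. Selective loss gives about 0.05 to 0.17 points against 1.1, assuming 5 to 20% lost from one sequence and 1 point per SD. A baseline shift of 0.5 points, also assumed, would give 0.25 before adjustment. Bias from selective loss needs loss that differs by sequence and is related to period change or treatment response. Unequal loss would also weaken the period-by-treatment check. The document gives no loss rate, so these figures illustrate scale and do not predict the result. The text does not support a claim that patients are in fact told early, or that the trial result is certain to be biased.

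**What to change.** Restate the sequence of steps as: phone screen; written consent; eligibility confirmed; baseline mobility, cognition and imaging completed; REDCap allocation released; trainer notifies the patient. People who decline or fail before baseline are then screening losses, and pre-baseline loss from the randomised set is nil by construction. Losses after baseline, and any unblinding of testers at the mid and post tests, are not affected.

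The cost is mainly logistic. Classes hold six people and blocks hold twelve, so allocation released after baseline leaves shorter notice for filling classes and could delay a cohort's start. Holding provisional class slots from the phone screen onward would ease this. No extra visits or patients are needed.

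If the order cannot change, state that the trainer will not disclose the sequence until baseline is complete, and report losses between allocation and baseline by sequence. This prevents refusal and baseline effort from responding to a known sequence, although the lost patients would still have no baseline.
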